### ***Satisfaction***

Satisfaction scores will be summarized and presented as mean scores per month per site.

### ***Receipt of follow-up mental healthcare***

Descriptive statistics (e.g. frequencies, proportions) will summarize the number of children/youth who received and did not receive follow-up care.

### ***Process Outcomes***

Descriptive statistics (e.g. frequencies, proportions) will summarize process outcomes per month, which will be analyzed as described above for the wellbeing and functioning outcomes. Length of ED stay will be expressed as mean time (with interquartile range) and analyzed using segmented regression as described for the primary outcome (wellbeing).

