# 1. OVERVIEW

## 1.1 Need for improvement

For people in acute mental health or addictions crisis, Alberta's emergency departments (EDs) are vital navigational and safety net hubs for assessment, treatment and referral to specialized services. In the past 3 years alone, the annual number of ED visits in Alberta has increased by 16% for children and youth seeking mental health and addictions care (from 10,977 visits to 12,702 visits). The greatest numbers of visits occur in Alberta's two children's hospitals—in 2017, EDs in the Alberta Children's Hospital and the Stollery Children's Hospital saw 2,406 and 2,397 visits, respectively, for mental health and/or addictions concerns. This study focuses on improving care in these two EDs and their connections to community-based follow-up after the ED visit.

Child and youth mental health and addictions crises vary. Common reasons for seeking ED care are suicidal intentions, panic attacks, illicit drug use, and aggressive behaviours that risk hurting others. For children, youth and their families, these crises are stressful, can be overwhelming, and leave the family vulnerable. In response, acute care must be specialized and multidisciplinary. To be more than a temporary patch, this care must also integrate with broader services such as primary healthcare and community- and school-based services. Current clinical care and health system gaps in Alberta, however, prevent many children and youth from receiving specialized and integrated care.

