### ***Process/health system outcomes***

In this project, we will access administrative healthcare data for participant ED visits. ED data will be reviewed for participants who consent/assent to medical record review. We will measure the following outcomes:

- Number of children/youth per month discharged ASQ at triage (low-risk screening outcome) to urgent care follow-up clinic
- Number of children/youth per month who receive psychiatry consultation in the ED after HEADS-ED assessment
- Number of children/youth per month discharged to urgent care clinic after HEADS-ED assessment
- Number of children/youth per month discharged with another recommendation after HEADS-ED assessment, and documentation of the recommendation
- Number of ED visits per month for child/youth mental healthcare that concluded in admission to each children's hospital or transfers to admit at another institution
- Length of ED stay (the interval between time of ED arrival and time of ED departure, either admission or discharge; in minutes) for visits per month to each children's hospital
- Proportion of discharged children/youth who received urgent care clinic follow-up within 48 hours
- Number of child/youth receiving follow-up mental healthcare within 7 days of the ED visit (to be reported by parents/caregivers at 1-month follow-up)
- Number of child/youth receiving follow-up mental healthcare that relates to their index ED visit, within 7 days and 1 month of the index visit
- Appropriate care in the appropriate setting. Research assistants will audit all ED/clinic records monthly at each site and document whether assessments children/youth received are congruent with discharge recommendations
- Type of follow-up care accessed. Parents/caregivers will report types of follow-up care within a month after an ED visit or urgent clinic follow-up appointment

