### ***Administrative***

Daily medical record review by research assistants will include collecting data on the number of bundle-eligible children/youth, number of children/youth with urgent clinic appointment booked based on ASQ screen at ED triage, and HEADS-ED assessment outcomes. Administrative databases will be accessed to collect: length of ED stay, time of admission to ED, time of discharge from ED, the Canadian Triage and Acuity Scale (CTAS) and the number of children/youth who received urgent care clinic appointment within 48 hours. Also, data will be collected for any ED visits within 30 days of the participants' index ED visit including the re-presentation visit triage date and time, the chief complaint, admission status, CTAS score, and discharge diagnosis. The Calgary team will access Edmonton's site participants' ConnectCare for the data collection within 30 days of the index ED and also the CTAS score from the index ED visit.

The PI will provide the full name, age, and Alberta personal health number (PHN) of study participants enrolled in the pre-implementation bundle and post-bundle implementation periods with Alberta Health to enable linkage to administrative healthcare databases in the economics analysis project (e.g., NACRS, ACCS, DAD, Alberta Health, Coroners' Data).

To enable the analysis in the economics sub-project, the PI will provide investigators at the Institute of Health Economics with study participants':

1. Study screening ID (generated for study administrative purposes)
2. Date of enrolment (to confirm study phase)
3. Assigned cohort (pre-implementation or post-implementation; to confirm study phase)
4. Age and gender

5. Forward sortation data (participant disclosed 3 first digits of postal code) at time of enrolment

6. Well-being scores

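### Four process outcomes exist only once the bundle's tools are in use, yet the plan sends them to a before-after segmented regression; the other counts have no fixed denominator

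*Protocol*

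**What the plan says.** Protocol 3.8 (Process/health system outcomes) lists 11 outcomes. Seven are worded as a number of children or visits, one is a duration (length of stay), one is a proportion (clinic follow-up within 48 hours), and two concern appropriateness and type of care. The first four presuppose a bundle tool. One rests on the ASQ: "Number of children/youth per month discharged ASQ at triage (low-risk screening outcome) to urgent care follow-up clinic". The other three are counted after HEADS-ED. They cover discharge to the urgent care clinic, discharge with another recommendation, and psychiatry consultation, the last worded as "Number of children/youth per month who receive psychiatry consultation in the ED after HEADS-ED assessment".

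On the population, the same section states that "ED data will be reviewed for participants who consent/assent to medical record review". Section 3.9 (Administrative) adds: "Daily medical record review by research assistants will include collecting data on the number of bundle-eligible children/youth".

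On analysis, 3.11 (Process Outcomes) says that descriptive statistics will "summarize process outcomes per month, which will be analyzed as described above for the wellbeing and functioning outcomes". It makes no exception for any outcome. The model referred to has a baseline level, a pre-intervention trend, and changes in level and trend for each later phase. Under 3.11, a change in intercept or slope from the pre-intervention to the maintenance phase counts as strong evidence of an intervention effect. A separate subsection of 3.11 on receipt of follow-up care says only that descriptive statistics "will summarize the number of children/youth who received and did not receive follow-up care".

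**The concern.** An interrupted time series compares what happened after a change with what the earlier series would have predicted. It needs an outcome that could have been observed before the change. Sections 2.1 and 2.2 introduce the ASQ and HEADS-ED as parts of the bundle, and 2.4 describes a 12-month pre-implementation phase without active innovations. For four outcomes the earlier series is therefore empty, or zero by definition. Testing a change in level then asks whether the tools were introduced, which is already known.

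The other three counts (admissions or transfers, and two counts of follow-up care) do exist in every phase. A bare count, however, rises and falls with the number of people enrolled. If consent or recruitment differs between phases, the count moves while care stays the same. The 7-day follow-up count reported by parents also depends on response at 1 month.

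At stake is the reading of these process results. Under the plan's own rule, tool uptake or enrolment drift could be reported as evidence that the bundle changed care.

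**Working it through.** **The plan's own volume figure.** Section 1.1 gives 10,977 rising to 12,702 visits: 12,702/10,977 − 1 = 15.7%, which rounds to the stated 16%, or about 5.0% a year over 3 years. It is used below to test whether volume growth matters.

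**Inputs from the protocol.**
- Phases of 12 + 5 + 12 = 29 months (2.4).
- About 200 visits a month per site: 2,406/12 = 200.5 and 2,397/12 = 199.8 (1.1; 3.10 gives 150 to 200).
- About 20% ineligible (3.5), so 200 × 0.8 = 160 eligible a month.
- Consent 75% (3.10), so 160 × 0.75 = 120 participants a month.
- Two-sided 5% level (3.10).

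**Assumptions not in the protocol.** Event risk 0.2, independent months, and the size of any drift in consent.

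**Model.** The 3.11 segmented model, fitted by ordinary least squares: level, trend, and level and trend changes for implementation and for maintenance. The result recorded is how often the maintenance level change is significant. Repeat simulations agree within one or two percentage points.

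**1. Tool-defined outcomes.** All 12 baseline months are zero; after that a fraction of participants follow the pathway.

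| Fraction following the pathway | Runs flagging a level change |
|---|---|
| 5% | 87% to 89% |
| 10% | 99.9% |
| 20% or more | 100% |

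No denominator changes this, because there is no baseline value to compare with.

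**2. Other counts, no true effect, consent falling in maintenance.** The expected monthly count is 160 × consent × 0.2.

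| Consent in maintenance | Expected count | False positives, raw count |
|---|---|---|
| 75% | 24.0 | about 5% |
| 65% | 20.8 | 9% to 10% |
| 55% | 17.6 | about 23% |
| 45% | 14.4 | 44% to 45% |

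A start-up ramp from 35% to 75% consent over the first 4 months gives about 30%.

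**3. Which denominator works.** Dividing by that month's consenting participants keeps the rate at 4.2% to 6.1% in every scenario. Dividing a consenter-only numerator by all eligible visits does not help. A fall from 75% to 65% still lowers the ratio by 1 − 65/75 = 13.3%, and false positives stay at about 10% to 48% for falls to 65% through 45%.

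**4. Steady volume growth.** Growth of the size in 1.1 gives 4.5% to 5.8% false positives on counts, which is about nominal, because the pre-intervention trend absorbs it. Only an abrupt 16% step at maintenance raises the rate, to 9.4%.

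**The case against.** The strongest reply is that offsets, denominators and the choice between linear and count models usually belong in a statistical analysis plan, which is not shown. Section 3.11 also calls its model anticipated and open to refinement after plotting, and it names proportions among its summaries. For the secondary point much of this stands: it is a caution, and 3.10 assumes the same 75% consent in every phase. It does not answer the main point. The protocol itself assigns these outcomes a model that needs a pre-intervention series, and no refinement can supply one.

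The population is also less settled than one sentence in 3.8 suggests. Section 3.9 has daily record review collecting numbers of eligible children, ASQ-based bookings and HEADS-ED results, and 3.8 mentions an audit of all ED and clinic records. This is an ambiguity to resolve, not proof that only consenters are counted.

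A reader might infer three stronger things that the documents do not support.
- *All process outcomes are raw counts.* Seven of 11 are. Length of stay and the 48-hour proportion are not.
- *Rising ED volume will create effects.* Section 1.1 does report that "the annual number of ED visits in Alberta has increased by 16% for children and youth", but that is province-wide and steady growth is absorbed by the trend term.
- *Objective 4 would rest on tests whose null cannot be true.* Section 1.2 defines that objective by length of stay, access and time to follow-up, and ED revisits. It names none of the four tool-defined counts.

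On receipt of follow-up, the specific subsection can be read as overriding the general one. The overlap needs a clarifying line but is weak as a contradiction.

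**Conclusion.** The main point holds without any assumption about drift. Four of 11 process outcomes have no pre-implementation series, and the plan makes no exception for them. Once the tools are in ordinary use, a significant level change is close to certain and says nothing about benefit.

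The secondary point is a risk whose size depends on assumed drift. It is modest for a 10-point fall in consent (9% to 10% against 5%) and serious for falls of 20 to 30 points (about 23% and 44%). These figures rest on event risk 0.2, independent months and 120 participants a month at baseline.

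The 1-month wellbeing outcome is a mean score, not a count, and lies outside this point.

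**What to change.** In 3.11 (Process Outcomes):

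1. Report the four ASQ/HEADS-ED outcomes descriptively, as uptake of the bundle.
2. Limit segmented regression to outcomes defined in all phases, for example admission, length of stay, and psychiatry consultation of any origin.
3. Analyse the remaining counts as proportions with numerator and denominator from the same population. Use that month's consenting participants or, for 7-day follow-up, those with 1-month data. Use all bundle-eligible visits only if the numerator also covers all eligible visits. Fit a binomial model, or a Poisson model with the matching offset.
4. State in 3.8 which population each process outcome covers.
5. State whether the subsection on receipt of follow-up or the one on process outcomes governs the analysis of follow-up care.

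The cost is minor rewording when consenting participants are the denominator. The downside is that such rates describe consenters only, so a change in who consents could still shift them. Covering all eligible visits would avoid that where the records allow, but may need ethics agreement to aggregate counts. It cannot supply the parent-reported 7-day outcome for non-participants.

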### ***Health Economic Analyses (separate project)***

Health economic analyses will combine data on costs of resource use with outcomes on child/youth wellbeing to determine if our care bundle is cost-effective and gives value for money for public payers. The analyses will use SCWBS/WEMWBS scores to measure the benefit of our care bundle. Incremental cost and wellbeing outcomes will be combined to calculate incremental cost-effectiveness ratios. The change in costs minus cost of implementing the bundle will be reported as a return on investment statistic. Uncertainty will be addressed with bootstrap analyses.

We considered a range of quality of life measures but found them unresponsive to changes in mental health in our population, either because mental health items were limited or those included were not relevant to crisis situations. Although the absence of a suitable preference-based quality of life measure means that quality adjusted life years (QALYs) cannot be included in the analyses, recent reports describe how wellbeing can be valued and compared to QALYs. Novel approaches emerging from that research will be incorporated into our analyses. Economic analyses will focus on secondary care health service use. Administrative- and individual-level data will be linked to provincial cost data to establish costs for participants who received care in the pre-implementation and maintenance phases. Although our care bundle is likely to have an impact on primary care health services and other areas of public expenditure, the scope of this project does not permit us to measure the impact of the bundle on areas outside of health; assigning costs to those outcomes would be problematic.

Individuals at the Institute of Health Economics will perform an economic analysis of the intervention by comparing the healthcare resource use and costs during the pre-bundle implementation period and post-bundle implementation period. The economic analysis will use administrative data (**hospitalizations, outpatient visits, and physician claims, between January 2020 and June 2022; and population registry data between April 1, 2019 and March 31, 2023**).

## **4. COMMUNICATION PLAN**

The communications plan, outlining our efforts and recruit participants for this project, will be led by the project lead, co-lead, and operational leads for clinical care settings. The project manager will operationalize the plan, as it will be linked to the project timeline and change management plan. The communications objectives are outlined below by study year.

## 4.1 Year 1

1. Increase understanding among ED and clinic healthcare providers of the project's purpose, how the bundle will be introduced, its impact on workflow/roles/responsibilities, and its benefits
2. Establish lines of communication with partners (primary healthcare, school- and community-based services) and families on how the bundle enhances healthcare availability/access, will be evaluated, offers families opportunities to participate in evaluation, and enables inter-agency collaborations
3. Develop communication strategies for partners and families by consulting on stakeholder communication preferences

To facilitate meeting these key objectives, operational leads will hold quarterly meetings with healthcare providers to discuss and optimize the bundle. Practical training sessions on bundle components (e.g., ASQ and HEADS-ED, CAPA) will be held between meetings, which allow us to collect input from healthcare providers. In partnership with stakeholder team members, operational leads, and patient partners we will host webinars and develop project communication materials. We will create and test plain language materials for families.

## 4.2 Year 2

Year 2 will focus on communication strategies for bundle implementation:

1. Among healthcare providers: introduce change management process maps, discuss resistance to change, and review key performance indicators from PDSA cycles
2. Among partners: refine strategies for communication and collaboration based on Year 1 experience and feedback
3. Among families: clarify bundle misconceptions/misunderstandings by refining community engagement campaign (e.g., online media, posters, print materials)
4. Among team members and collaborators: maintain regular communication between on project progress, milestones and input

The focus will be on implementing change management plans and PDSA cycles, and obtaining feedback from children, youth, and parents during PDSA cycles on the bundle, as well as holding regular team meetings and obtaining feedback from partners on the strength of partnership and communication. In the bundle maintenance phase (part of Year 2 and Year 3), key to communication will be sharing results and recommendations in real-time to share progress being achieved.

## 4.3 Year 3

1. Create products tailored to stakeholders that communicate results and recommendations
2. Share finalized change management documents
3. Hold meetings to discuss potential province-wide bundle deployment (e.g., eligible EDs, AMH SCN, ESCN)

# 5. PATIENT ENGAGEMENT

Patient engagement is central to this project. We are using Amirav's adaptation of the International Association of Public Participation Spectrum of Engagement for health research and the CIHR-SPOR Patient Engagement Framework as the basis for our evidence-informed approach to engagement. These resources and our consultation with [name] (Patient Engagement Platform, Alberta SPOR SUPPORT Unit) shaped an engagement framework that guides team activities.

Youth and parents/caregivers are rarely engaged meaningfully across the research continuum. In contrast, as core members of our team, patient partners will help oversee bundle introduction to EDs, interim data analyses, and Plan-Do-Study-Act (PDSA) cycles, all of which will have a strong focus on learning from family experiences during initial implementation. Patient partners will also be involved in governance activities (see Section 7.0 for further details) and key knowledge translation (KT) activities—to incorporate their perspectives, they will help write project reports and updates that will be distributed to partners and stakeholders.

## 6. CHANGE MANAGEMENT

In consultation with AHS Change Adoption & Evaluation, we will apply the ADKAR® model to prepare for change. The Prosci ADKAR® Model is a goal-oriented change management model that guides individual and organizational change. ADKAR is an acronym that represents the five tangible and concrete outcomes that our team will follow to achieve lasting change: *awareness, desire, knowledge, ability, reinforcement*. By outlining the goals and outcomes of successful change, the ADKAR Model will equip our team's leaders to facilitate institutional change, and it will support our team members and the effected healthcare providers at all study sites throughout the change. PRIHS funding will support Change Management Leads in Calgary and Edmonton with the knowledge and abilities to implement our care bundle. Change management teams incorporate a Lead, Change Specialist, project team members and champions—ED and clinic managers, patient care managers, nurse educators, and senior leaders.

Below, we use of Normalization Process Theory (NPT) as a framework to guide change and 'normalize' the bundle into routine acute mental health and addictions care of children and youth. NPT is used to support implementation of complex clinical interventions and new care collaboratives—our project features both these aspects. It includes four constructs for the work that is required to fully implement a set of new practices: coherence, cognitive participation, collective action, and reflexive monitoring. Each construct is a distinct phase of implementation. Our approach will be non-linear—while we will begin with coherence and continue through the phases sequentially, we will revisit constructs to address project needs and challenges that occur over time.

### 6.1 Phase 1: Coherence (Year 1)

The milestone for Phase 1 includes establishing awareness of the proposed bundle of care. Change Management Leads will support and coach all management levels, overseeing integration of change management activities. Change Specialists (reporting to Leads) will complete all change management deliverables. Specialists will work with champions on training plans and change management strategies, identifying how the care bundle will impact individuals, what the bundle expects from each stakeholder group, how to support each group for change, and roles of champions. The strategy will be developed in Year 1, informed by champions' identification of risks, barriers, and enablers to introducing and supporting the care bundle in AHS, and supported by a change management communication plan. Each Change Specialist and their change team will create change management process maps, champion roadmaps, coaching and training plans for frontline providers along with a resistance management plan to facilitate awareness, desire, and knowledge.

We will establish awareness among healthcare providers, managers, directors and administrative staff in:

- Alberta and Stollery Children's Hospital EDs
- Existing AHS children's mental health clinics (1.5 in Calgary; 4 + 2 x 0.5 in Edmonton and surrounding area [6 clinics with 0.5 to 1.0 availability])

- Mental health and addictions services offered in primary care, schools, community-based and non-profit organizations

